### Outcomes

#### Primary outcomes

Principal variables in the pregnancy are iron status of the mother at each clinical visit (anemia, ferropenic anemia, risk of hemoconcentration) and birth weight of the baby.

Definition of main outcome variables

– Anemia is defined as Hb <110 g/L in the 1st and 3rd trimester, Hb <105 in 2nd trimester, Hb <120 g/L post-partum [21].

– Ferropenic anemia is defined as: Hb < the normal limit, and serum ferritin (SF) <15 μg/L [22].

– Hemoconcentration risk is defined as: Hb >130 g/L in the 2nd and 3rd trimester [4].

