#### Analysis of the primary outcome

The effects of iron dose supplement in each RCT on the biochemical iron status and mother-child health will be compared using regression models adjusted for those variables that can influence the relationship. Logistic regression or Cox models will be applied for qualitative variables such as, for example, the percentage of anemia or hemoconcentration at the end of pregnancy. Linear multiple regression models will be applied for dependent quantitative variables. The models will be adjusted for those variables that biologically affect the relationships studied, such as the serum ferritin levels, presence of alterations in the HFE gene, age of the mother, gestational age, parity, anthropometric indices, diet, and lifestyle, and the interactions between these variables. Initially included in the model will be all those variables that form part of the theoretical model and, in a second phase, the variables for entry into the model will be selected step by step (forward and backward) to achieve the most reduced stable models.

Conditions for the application of models will be verified using standard techniques that are based, essentially, on residuals analysis. The bilateral null hypothesis of normality, no difference, and non-significance of the regression coefficients, will be rejected when their probabilities are <5%. The data will be analyzed using the latest version of SPSS/PC package for Windows.

Data will be analyzed in 2 ways:

a) Intention-to-treat analysis

The principle of “intention-to-treat” is a way of analyzing the results that considers all individuals entered into the study, according to the group to which they were originally assigned, although they may not have complied with the protocol. In this case, in all the circumstances that have led to not having hemoglobin determinations before delivery, we will proceed to incorporate at this time-point the immediately-prior determination of hemoglobin. All randomized participants randomized who had received at least one dose of study medication will be included.

b) Per-protocol analysis

Included in the analysis will be only those pregnant women who received the allocated intervention at randomization. The per-protocol population (PP) will include those participants who had taken at least the 80% of the study medication, with proper assessment of adherence, or without any major protocol violations.

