Pregnant women diagnosed with anemia at the start will be treated according to the usual protocol, and not as a part of the current study. Women diagnosed with anemia posteriorly, will be treated with standard therapy, but will remain part of the study in the intention-to-treat analysis. However, they will not be considered in the per-protocol analysis.

Data missing from the study variables will be treated with the direct likelihood method [34] when no data is available. In these cases, the profile of pregnant women will be used to adjust the estimates of these parameters.

An analysis of sensitivity will be performed using a mixed model based on constraint-based patterns of missing values without dependence on the future to assess the robustness of the main results of the Mixed Model Repeated Measures against the possible transgression of random default assumption.

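### The primary models and the missing-data sensitivity analysis imply different main analyses, so robustness of the primary results to the planned 35% drop-out is not established

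*Protocol article*

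**What the plan says.** All references are to the protocol article.

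- **Primary outcomes** lists "iron status of the mother at each clinical visit (anemia, ferropenic anemia, risk of hemoconcentration) and birth weight of the baby". The iron-status items are yes/no classifications by cut-off: "Anemia is defined as Hb <110 g/L in the 1st and 3rd trimester", with other limits for the second trimester and post-partum; ferropenic anemia adds a serum ferritin limit; and "Hemoconcentration risk is defined as: Hb >130 g/L in the 2nd and 3rd trimester". Birth weight is quantitative and measured once.
- **Analysis of the primary outcome** gives the models: "Logistic regression or Cox models will be applied for qualitative variables", with anemia and hemoconcentration at the end of pregnancy as the examples, and "Linear multiple regression models will be applied for dependent quantitative variables". No mixed or repeated-measures model is listed there.
- **Intention-to-treat analysis**, in the same section: where Hb before delivery is missing, the plan will "incorporate at this time-point the immediately-prior determination of hemoglobin".
- **Closing paragraphs of that section** (after the per-protocol analysis): missing data are to be handled by direct likelihood, and a mixed model with pattern constraints that exclude dependence on the future is to "assess the robustness of the main results of the Mixed Model Repeated Measures against the possible transgression of random default assumption".
- **Participant withdrawal**: women who become anemic during the trial stay in follow-up and count as therapeutic failures in the intention-to-treat analysis.
- **Sample size** allows for 35% drop-out.

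**The concern.** The model whose main results are to be stress-tested is not among the models assigned to the primary outcomes. The missing-data method that goes with it, direct likelihood under missing at random, is also not the carry-forward rule of the intention-to-treat analysis. A statistician following the text could treat either set as primary.

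If the logistic, Cox and linear models are primary, their results get no stated check against data missing not at random. The per-protocol analysis changes the population and does not fill that gap. At stake is whether a difference between doses in the percentage with anemia or hemoconcentration, or in birth weight, can be trusted when about a third of the women may leave.

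**Working it through.** **1. The two sets of rules side by side**

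| | Models listed for the primary outcomes | Closing paragraphs of the same section |
|---|---|---|
| Threshold outcomes | logistic or Cox regression | mixed model for repeated measures, response not stated |
| Birth weight | linear regression | not mentioned |
| Missing Hb before delivery | previous Hb carried forward | direct likelihood for missing study variables |
| Check against departure from missing at random | none stated | pattern-constrained mixed model, aimed at the repeated-measures model |

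The repeated-measures model is named only in the sensitivity-analysis sentence. Its response, visits and covariates are not given.

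**2. What such a model could support**

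An ordinary mixed model for repeated measures takes a repeated quantitative response. Hb is the natural candidate, but the article does not say so. On that assumption, stability of the estimated Hb means bears only indirectly on the percentages beyond a cut-off. It bears on birth weight not at all.

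**3. How the 35% enters the plan's own sample size**

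Inputs from the Sample size section: one-sided alpha 0.05, power 0.80, a 10-point reduction from 23.5% (Stratum 1) and from 14.7% (Stratum 2). The arcsine formula is n = 2[(1.645 + 0.842)/h]², with h = 2·arcsin√p1 − 2·arcsin√p2.

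- Stratum 1, 23.5% v 13.5%: n = 183.3, rounded up to 184; 184/0.65 = 283.1. The plan states 283.
- Stratum 2, 14.7% v 4.7%: n = 101.0; 101/0.65 = 155.4. The plan states 156.

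So the stated sizes already include the drop-outs. The planned losses are:

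- Stratum 1: 0.35 × 283 = 99 per arm
- Stratum 2: 0.35 × 156 = 54.6, about 55 per arm
- Overall: 0.35 × 878 = 307 women

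**4. How much the drop-outs could matter (illustration)**

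Assume 35% lost in each arm, the outcome unknown in all of them, and the planned 10-point difference in completers. With d the difference in drop-outs, the overall difference is 0.65 × 10 + 0.35 × d.

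- d = 10: overall 10 points
- d = 0: overall 6.5 points
- overall zero: d = −6.5/0.35 = −18.6 points

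**5. Why the carry-forward rule needs its own check**

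Suppose the last available Hb is still the value that placed the woman in her stratum. In Stratum 1 that value lies between 110 and 130 g/L, so carrying it to the third trimester makes her neither anemic nor hemoconcentrated, whatever her dose. In Stratum 2 it exceeds 130 g/L, so she is classed as hemoconcentrated, whatever her dose. For such women the rule sets the difference between doses to zero by construction (d = 0 in step 4). Testing a different model against departure from missing at random does not examine that assumption.

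**The case against.** The strongest defence is that iron status is primary at each clinical visit, so a repeated-measures model is not out of place. The section compares the doses on biochemical iron status and provides for quantitative dependent variables. A mixed model can also be fitted to repeated yes/no data. An article may leave the choice of response to the full protocol or analysis plan.

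The two missing-data rules might also be meant to share the work: carry-forward for Hb before delivery, and direct likelihood where nothing else is available.

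Much of this stands. A reader might infer that the mixed model is a test of mean Hb, that it therefore fits none of the primary outcomes, and that its result says nothing about them. The article does not support that: the response is not stated, a model for repeated binary data is conceivable, and a model on Hb gives indirect evidence. Nor can one assert that the mixed model is not the primary analysis, since the article itself calls its results main. Comparing the power of a mean-Hb test with that of a test of percentages on complete data would not help either, because such a comparison contains no missing-data mechanism and can be made to agree or disagree by the choice of scenario.

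What does not stand is the appeal to an unseen document for the whole matter. The article states both sets of models and both missing-data rules, and they do not match. Birth weight is left without a check under every reading.

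**Conclusion.** The point holds as an inconsistency between stated rules, and it should be corrected before analysis. The article implies two different main analyses and directs its only missing-data sensitivity analysis at the one it never defines. As written, that analysis does not establish whether the primary logistic, Cox and linear results, or the carried-forward Hb values behind them, are robust to drop-out.

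The planned drop-out is about 99 of 283 women per arm in Stratum 1 and 55 of 156 in Stratum 2. The 18.6-point figure is an illustration. It rests on equal drop-out in both arms, no outcome data after drop-out, and the planned 10-point difference in completers. It is not a forecast: a discontinuation visit with a blood sample is foreseen where possible, so fewer outcomes may be missing.

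The conclusion about the text does not depend on these assumptions or on what response the mixed model takes.

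**What to change.** Reconcile the two parts of Analysis of the primary outcome.

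1. Name one primary model for each primary outcome.
2. Name one primary missing-data rule: carried-forward Hb or a missing-at-random method.
3. Direct the sensitivity analysis at the results of those models and that rule, in place of the undefined mixed model.

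One way that keeps the plan's own approach is to multiply impute missing Hb and ferritin under missing at random, then again under the stated pattern constraints without dependence on the future. In each imputed data set, apply the cut-offs of Primary outcomes at each visit analysed, including post-partum, refit the primary logistic model and pool. Women already diagnosed with anemia should remain therapeutic failures, as Participant withdrawal states; that status should not be imputed over. Missing birth weight can be treated likewise with the linear model.

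The cost is revised wording and some extra programming. No new data or participants are needed.

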### Monitoring

To ensure correct conduct and security of the RCT according to the requirements of good clinical practice, external services will be contracted to perform the tasks of monitoring of the participating centers according to the requirements of the Spanish Agency of Medicines and Health Products [*Agencia Española de Medicamentos y Productos Sanitarios; AEMPS*].

### Harms

All adverse events suffered will be recorded at each clinical visit and assessed for severity, expectedness and causality.

### Ethics and dissemination

#### Research ethics approval

In Spain, approval was obtained from the Clinical Research Ethics Committee of the Jordi Gol Research Institute in Primary Care *[Instituto de Investigación en Atención Primaria; IDIAP]* and from the Spanish Agency for Medicines and Health Products *[Agencia Española del Medicamento y Productos Sanitarios; AEMPS]*.

The study is designed according to the requirements of the Declarations of Helsinki, and the Tokyo update.

### Consent

All participants are informed of the study, its objectives and activities related to their participation: number and schedule of visits, diagnostic tests, results information. Patients will be provided with detailed information leaflets, and will be asked to sign a consent form.

### Confidentiality

Confidentially will be guaranteed for all participants in the study. The study conforms to the Government Data Protection Act for Personal Information (15/1999 of 13th Dec. LOPD).

### Access to data

All documents will be stored securely and accessible only to trial staff and authorized personnel.

### Dissemination policy

All scientific publications must have the approval of the principal investigator (VA).

The principal investigator of the study is committed to making public such results as become available, both positive and negative. When studies and research are made public to the scientific community, the funding sources and the laboratory TEDEC-MEIJI FARMA S.A will be acknowledged.

The researchers are committed to making raw, anonymity-guaranteed, data sets available to the scientific community upon legitimate request to the principal investigator, once the trial is completed.

## Discussion

The ECLIPSES randomized clinical trial is an intervention study in Primary Care directed towards pregnant women. It attempts to establish the optimum iron supplementation to prevent not only iron deficit but also iron excess during gestation. The approach used is to adapt the standard supplementation to the individual characteristics of the pregnant woman, based on the hemoglobin level at the start of gestation.

Prevention is important, given the elevated percentage of anemia during pregnancy (around 25%) and of the risk of hemoconcentration (around 15%); conditions which have been associated with adverse effects not only in the mother but also in the newborn.

We will take the following measures to minimize, or avoid, bias in the conduct of the trial:

– Randomization: An externalized randomization program will be used to ensure allocation concealment

– Use of an electronic data collection system that enables homogeneous data collection and reduces transcription errors

– External RCT monitoring, which would increase the reliability of the results

– Blinding and assessment of outcomes: Iron supplements administration would be blinded. Therefore, neither the investigators nor the participants in the study nor the statistician would know the dose of iron in each of the treatment groups.

– Combined batched analyses of samples at the end of the study. The samples will be stored at -80°C in the Hospital’s BioBank and analyzed together at the end of the study, thereby limiting the potential bias that could be introduced by several different analytical procedures and laboratory personnel turn-over in the course of the trial. Further, inter- and intra-assay coefficient of analysis will be calculated for all of the measurements performed.

– Standardization of the activities of the health-care professionals involved in the different aspects of the study. Before starting the study, all the health-care professionals participating in the study will standardize their procedures so as to ensure that all the tests and/or questionnaires are conducted in the same manner.

The particular challenges that we anticipate in this study are as follows:

– Loss to follow-up. We hope to reduce this by taking advantage of the clinical visits that the pregnant women would normally have with her gynecologist/obstetrician. As such, she would not be required to undertake additional activities/visits by participating in the current trial. Further, we have increased the study sample size so as to compensate for possible loss to follow-up.

– The supplementation with iron can produce gastrointestinal side effects that can affect the adherence to treatment. To reduce this effect, the principal component of the supplement will be ferrimanitol ovalbumin which has been shown to have greater bioavailability and better tolerance than ferrous sulfate.

– It is difficult to know the adherence to the prophylactic iron supplement. To improve the registry, we will apply a semi-structured questionnaire on the degree of adherence to the prescription in all the clinical visits during pregnancy. This will indicate the number of units that have been returned to the investigator each week.

A primary strength of the study is its rigorous methodology that involves a large number of health-care professionals and patients, which will strengthen the validity of the findings. Conclusive outcomes would help the obstetrician in deciding the best iron supplementation pattern required to promote maternal and infant health. Initial hemoglobin levels that are routinely collected on all pregnant women attending the clinic, and there will not be any additional procedures that could dissuade participation by the pregnant woman.

Our findings would contribute to developing guidelines for good clinical practice.

## Abbreviations

Drugs_Q: Multi-vitamins and iron supplements questionnaire; EITQ: Early infancy temperament questionnaire; EPDS: Edinburg postnatal depression scale; Fagerstrom_Q: Fagerstrom questionnaire; FFQ: Food frequency questionnaire; Hb: Hemoglobin; ICS: Catalan institute of health; IPAQ: International physical activity questionnaire; PCC: Primary care centers; PSI: Parenting stress index; RCT: Randomized clinical trial; RHS: Reproductive health-care services; STAI: State-trait of anxiety inventory.
